***Quality control/assurance:***

A pilot transfer of patient medical data will occur prior to collection of study data to work out any issues with the data transfer process. The data manager will run data consistency and error checks after receiving the data from each facility at the three points of patient medical data transfer. If there are issues with the data, these will be communicated to the PI, who will in turn inform the facility staff until the issue is rectified. The online systematic observation instrument will help ensure that observational data are collected consistently. Quality assurance for the observational data will include training of observer to follow the observation protocol, training the observerto use the online observational data collection instrument correctly, and practicing using the instrument. The Beta-Test Manager will monitor the data as it is collected, check for any issues, and re-train observer if any issues are found.

***Data analysis plan, including statistical methodology and planned tables and figures:***

Analysis of observational data: Patient engagement with the video during the first half of each assessment (i.e., all waiting room patients) will be analyzed qualitatively and separately for each of the six video segments (i.e., opening, three stories, and two animations). Codebooks for the content analyses will be developed after the data are received. Content analyses of the observations will look for number of patients who watch or ignore the segment and if the segment elicits any positive or negative responses. Relationships will be sought between frequency of disengagement (i.e., number of patients who ignored or exhibited a negative reaction during a segment) and characteristics of the disengaged patients (i.e., apparent age, gender, race/ethnicity). Patient engagement during the second half of each assessment (i.e., four select patients) will be analyzed the same way; however, analysis will attempt to identify within segments the scenes that are associated with patient disengagement. In addition, data from the second half of the assessments will be evaluated quantitatively for estimated duration of engagement with each segment. Patterns of disengagement across the three facilities will be sought. We will use EZ-Text qualitative software to assist with our qualitative data analysis.

Analysis of patient medical data: For analytical purposes index visits are defined as a patient’s first HIV care clinic visit during a beta-test period (i.e., the historical comparison period or the intervention period). Patients may have index visits in both time periods. The index visit in each period will be time zero. Initiation of ART will be defined as the proportion of treatment-naïve patients (i.e., no previous record of an ART prescription) who are prescribed ART (as per the current treatment guidelines) on their index visit. Medication adherence will be defined as the proportion of patients prescribed ART who achieve viral load suppression (<50 copies/mL) at least 40 days after their index visit. Retention in HIV medical care is defined as the proportion of patients who are retained in care at 3 to 7 months of follow-up from their index visit. Partner protection will be assessed using a proxy measure—incident STDs. Incident STD is defined as the proportion of patients who do not have an incident STD as a function of time since their index visit. Incident STD is defined as a microbiologically confirmed STD diagnoses noted in patients’ electronic medical records (EMRs). Kaplan-Meier methods will be used to estimate the proportion of patients who achieve intervention outcomes. The analyses may be adjusted for patient-level covariates, such as age, race, gender, baseline viral load suppression, and baseline STD, as well as the three beta-test treatment facilities.

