**3. Systematic observation of select waiting room patients**

Observer will randomly choose four patients who have a clear view of the video, attempting to get a diverse sample regarding age, gender, and race/ethnicity. Patients who were not present in the previous cycle should be chosen, unless there are fewer than four patients in the waiting room who were not present during the previous cycle. If one or more of the four patients was present for the previous cycle, note this on the Survey Monkey instrument.

The observer will watch these four patients for one video cycle. Observer will begin this observation at the beginning of the video (i.e., Opening) and will continue this observation through each segment of stories or animation in the video for one full cycle of the video. The observer will record all reactions and behaviors that occur during each segment. For example, a patient may begin watching the video, have a negative reaction, and stop watching the video during a segment. If a patient is absent during one or more segments of the video during the cycle, the observer will check the “N/P” box for that patient’s reactions for those segments (e.g., if the patient leaves in the middle of a story, the observer will mark what occurred for that patient up until the time he or she leaves, and enter N/P for the rest of his or her segments). If there are fewer than 4 people in the waiting room to observe initially, the observer will enter N/P for the missing patients’ segments. However, if one or more patients subsequently enter the waiting room during this cycle, the observer should begin recording these patients.

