Replacements: If one or more replacements are needed, the observer will try to match the replacement demographics in terms of gender, race/ethnicity, and age (in that order). The observer should try to identify potential replacements at the beginning of the cycle in case they are needed. If any of the initial 4 patients being observed leaves, the observer will begin observing a replacement patient (and will add the replacement’s demographics to the instrument). The replacements will be numbered in the order in which they occur from 1 to 4. The observer should take care to remember which patient is which (e.g. choose #1 and go clockwise to #4). If one of the original patients comes back, the observer will stop watching the replacement at that point and go back to watching the original patient. The observer will mark N/P for any segments for which either a replacement or an original patient are not present.

The observer will use the time during the credits to note additional general observations for the cycle. The main point of this section is to note *in detail* any points in the video that seemed to hold attention, not hold attention, or elicit a particular reaction such as laughter, discussion, or disengagement with the video specifically for the patients observed.

If any patient notices appears uncomfortable, the observer should not choose them as an observation subject or should stop observing them immediately (and begin observing a replacement) if the observation has already begun. If any patients appear to be uncomfortable, the observer should record the event in summary comments.

The variables collected in this section include:

- Apparent age of each patient
- Apparent race/ethnicity of each patient
- Apparent gender of each patient
- The duration of engagement with video for each video segment
- Reactions and watching behaviors of patient during each video segment
- Information relative to engagement of the patients for this cycle

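### Replacements and late arrivals need not have a clear view of the video, so engagement by segment can reflect who was rated as well as what was shown

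*Protocol*

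**What the plan says.** **Analysis.** Under Analysis of observational data, the Data analysis plan states that engagement of all waiting room patients (the first half of each assessment) "will be analyzed qualitatively and separately for each of the six video segments". For the second half it adds: "Patient engagement during the second half of each assessment (i.e., four select patients) will be analyzed the same way". It also says that "data from the second half of the assessments will be evaluated quantitatively for estimated duration of engagement with each segment". Disengagement is expressed as a count: "number of patients who ignored or exhibited a negative reaction during a segment". The Design section makes the less engaging segments the ones to be changed.

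**Who is rated at the start.** Appendix 2, section 3: "Observer will randomly choose four patients who have a clear view of the video". It prefers patients who were not there for the previous cycle, unless fewer than four such patients are in the room. The Sampling section repeats the clear-view condition. Then: "The observer will watch these four patients for one video cycle".

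**Who is rated later.** When a patient leaves partway, "the observer will mark what occurred for that patient up until the time he or she leaves", and the remaining segments are coded N/P (not present). For the substitute, "the observer will try to match the replacement demographics in terms of gender, race/ethnicity, and age (in that order". That paragraph mentions neither view nor previous exposure. If fewer than four people are present at the start, those who come in during the cycle are recorded as they arrive, again with no condition on view. An original who returns displaces the replacement.

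**What the form keeps.** Appendix 3, section 3, has a row for each of four patients and four replacements in every segment. Item 3a records age, race/ethnicity, gender and presence in the previous cycle. It has no field for view. Item 2a counts people with an unobstructed view, but only for the room as a whole in the first half.

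**The concern.** The segments always run in the same order: Opening, Story 1, Animation 1, Story 2, Animation 2, Story 3. The Opening is rated mainly in people chosen for a clear view. Any later segment may be rated partly in people to whom that condition was never applied. Someone who cannot see the monitor will be scored as not watching, whatever the segment is like, and nothing on their row of the form shows why.

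Previous exposure raises the same question. The Bias section and the scheduling paragraph of Appendix 2 both treat it as something to keep down, yet the preference for first-time viewers is not carried over to replacements.

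At stake is Objective 1, finding the parts of the video that need refinement. If the people rated differ between segments, the segment chosen for re-editing may owe its place partly to turnover in the room.

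**Working it through.** **Step 1: the number followed.** Eight assessments at each of three facilities give 8 × 3 = 24, which agrees with the Bias section. The 32 in the Sampling section equals 8 × 4 and does not fit three facilities; this is a separate inconsistency to reconcile. Appendix 2 expects 6 to 8 assessments per shift, so 18 to 24 in all, and 72 to 96 initial select patients (18 × 4 to 24 × 4).

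**Step 2: the selection rules side by side.**

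| | Clear view | Not present in previous cycle | Demographics |
|---|---|---|---|
| Original four | required | preferred | diversity sought |
| Replacements | not stated | not stated | matched |
| Late arrivals | not stated | largely met, since they have just come in | not stated |
| Recorded per person on the form | no | yes | yes |

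Previous exposure can be examined afterwards. View cannot.

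**Step 3: how far the people rated could change.** The Protocol gives no leaving rate and no figure for engagement of replacements, so both are assumed. Let *h* be the share of originals leaving between segments, with every leaver replaced and none returning. The replacement share at the sixth segment is 1 − (1 − *h*)^5. With true engagement equal in all segments, and replacements differing from originals by *d* points, the apparent shift at the sixth segment is share × *d*.

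| *h* (assumed) | Replacement share | Shift if *d* = −20 | if *d* = 0 | if *d* = +20 |
|---|---|---|---|---|
| 5% | 1 − 0.95^5 = 23% | −4.5 | 0 | +4.5 |
| 10% | 1 − 0.90^5 = 41% | −8.2 | 0 | +8.2 |
| 15% | 1 − 0.85^5 = 56% | −11.1 | 0 | +11.1 |

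Returning originals would lower these shares.

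**Step 4: counts without a denominator.** Suppose 40% of 96 patients are disengaged in every segment and no replacements are available. The expected count is 96 × 0.4 = 38 at the first segment. At the sixth it is 38.4 × (1 − *h*)^5, or 30, 23 or 17 for *h* of 5%, 10% or 15%. On raw counts, the later segment looks more engaging although nothing has changed.

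**Step 5: originals alone are not free of selection.** Suppose half the originals watch with probability 0.9 and half with 0.3, so 60% watch at the first segment. If leaving is unrelated to engagement, 60% of those remaining watch at the sixth. If the less engaged leave at 15% per segment and the more engaged at 5%, it is 68%. With those rates swapped, it is 52%.

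**The case against.** A reader might infer that turnover builds in a drift against Animation 2 and Story 3. The Protocol does not support that. It gives no leaving rate, no reason for leaving and nothing on how engaged replacements are. The shift is zero if they are equally engaged and reverses if they are more engaged. Absence is coded N/P rather than as disengagement, and raw counts can favour later segments. Replacements may also enter early, and they are dropped when the original returns.

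A reader might also infer that summarising each segment separately is itself an error, because the same people are followed throughout. That does not hold either. Repeated ratings of one person do not bias the level reported for a segment; they bear on precision and on the chance to compare within a person. No test between segments is planned. Moreover, the sentence about separate analysis describes the all-patient half, which has no fixed four and no replacements; it reaches the select patients only through the statement that they are handled alike.

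The defence can add that the work is developmental, that codebooks are to follow, that denominators and N/P handling may be settled there, and that the observer notes obstructed seats at check-in and may well avoid them when choosing a replacement. All of this limits the weight of the point. What remains is a collection rule fixed in this document that drops a condition set for the original four, and a form that cannot show afterwards whether the condition was met.

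**Conclusion.** The point holds as a modest weakness in the observation rules and the segment summary. The original four are chosen for a clear view and, where possible, a first viewing. Replacements need meet neither condition, and late arrivals need not have a clear view. Differences between segments can therefore mix content with the people rated, and view cannot be recovered from each person's record.

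Neither the sign nor the size of the effect follows from the Protocol. The shifts of 4.5 to 11.1 points are illustrations that rest on the assumed leaving rates, on no returns and on an assumed 20-point difference. They show that the effect need not be negligible with at most 96 initial select patients; they do not predict it.

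**What to change.** **Appendix 2, section 3 (before observation starts).** Require a clear view for replacements and for late arrivals. For replacements, also prefer people not present in the previous cycle. Apply both before the demographic matching.

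**Data analysis plan.** Report engagement for each segment as a proportion of the patients present, leaving out N/P. Show originals separately from replacements and late arrivals. Add a descriptive comparison of segments within patients present for both, with a note that those who stay may differ from those who leave.

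**Cost.** A sentence or two in Appendix 2 and a short addition to the analysis text. The form already keeps a row per person for every segment, so these summaries need no new data. There will be somewhat fewer eligible replacements, and the within-patient summary will rest on fewer patients, most of all for segments far apart in the cycle.

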**Study design:**

***Location(s):*** The three HIV/AIDS treatment facilities where the beta-testing will take place are: 1) HIV Primary Care Clinic, Atlanta, GA; 2) AIDS Action Coalition, Huntsville, AL; and 3) the Borinquen Medical Center, Miami, FL.

The waiting room at the Borinquen Medical Center is not exclusively for HIV-positive patients; therefore, the video will be shown across the street in the Medical Center’s HIV case management office. The systematic observations will be conducted in the waiting room of the case management office, and patient medical data will be abstracted from Borinquen Medical Center’s EMR system.

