***Sampling, including sample size and statistical power:***

The sample for the systematic observation will be a convenience sample of all patients who are present in the waiting room during the 1 day of observation at each facility. A maximum of 8 observational assessments will be done at each facility (32 total assessments). Each observational assessment will consist of systematic observation of all waiting room patients during one video cycle and systematic observation of four waiting room patients during the next video cycle. The four patients will be chosen randomly among patients who have a clear view of the video with the intent of obtaining diversity regarding age, gender, and race/ethnicity. See Appendix 2 for the observation protocol for additional details. The unit of analysis will be the individual patients. We do not expect to revise the sampling estimates for the study.

The sample for the patient medical record data will include all HIV-positive clinic patients and their records during the historical comparison period and the intervention period. Simplified sample size calculations were performed for rejecting the null hypothesis of equality in the proportions of successes for a specific outcome, assuming equal numbers of patients in each period. These calculations correspond to an analysis using Fisher’s exact test with a two-sided significance level of α = 5%.

For the primary outcome of medication adherence (achieving viral load suppression at 6 months), if the true proportions of successes for the two periods are 70% and 77% (historical comparison to intervention, 7% absolute improvement, 10% relative improvement), then sample sizes of 650 patients prescribed ART per period will be required to have 80% power to reject this null hypothesis. Allowing for an annual attrition rate of 25%, then sample sizes of 1157 patients per period will be required to have 80% power to reject this null hypothesis.

For the secondary outcome of retention in care at 3-7 months of follow-up, if the true proportions of successes for the two periods are 75% and 82% (historical comparison to intervention, 7% absolute improvement, 9% relative improvement), then sample sizes of 566 patients per period will be required to have 80% power to reject this null hypothesis. Allowing for an annual attrition rate of 25%, then sample sizes of 1008 patients per period will be required to have 80% power to reject this null hypothesis.

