***Bias in data collection, measurement, and analysis:***

Biases with regard to the observation: Observation bias could affect the validity of the data. This bias will be minimized by having only one observer and training him to conduct the observation in a systematic fashion using an online instrument to guide the data collection, which will enhance observer consistency. Bias is also minimized by the data collection instrument requiring a low level of observer inference or interpretation of observed behaviors. In a waiting room patients are a collection of individuals and not participants in an interactive group, so the presence of a non-interacting observer should not influence patient behavior. Bias from expectancy effects will be offset by checking for correspondence between observed disengagement and medical outcomes addressed during segments when many patients were disengaged. There could be bias due to an inability of the observer to correctly recognize the HIV-positive patient characteristics (race/ethnicity, age, gender) or whether or not patients are truly engaged with the video or merely looking in the direction of the video screen. To a certain extent, this bias is inherent in the study design, and would be difficult to avoid without approaching the patients. Measurement bias could affect the generalizability of the data. Observations are limited to once per facility. Bias is minimized by conducting observations for eight hours, for a total of 24 assessments and an estimated 192 to 336 patients observed across all three facilities. The eight-hour observation period will minimize time-of-day bias but will be affected by day-of-week and month-of-year differences. Observations will be conducted during the first two months of the intervention period to minimize potential bias from previous exposure to the video.

Biases with regard to the patient medical data:

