**Appendix 2: Observation Protocol**

**Waiting Room Observation Protocol**

Scheduling: Systematic observations will be conducted within the first 3 months of the beta-test period to increase the likelihood that the patients being observed are seeing the video for the first time.

Checking in: At the beginning of the shift, observer will check in with the clinic manager, determine which video playback option is being used (i.e., continuous play, 10-minute interval between cycles, 20-minute interval), determine which waiting room seats do **not** offer a clear (unobstructed) view of a video monitor, and find a seat to begin the observation.

Finding a spot for the observation: Observer will find an open seat where he/she will be able to watch patients’ reactions from the most unobtrusive location possible. The patients should not be behind the observer. The observer may change positions if his/her position is not working well.

All data will be entered on a tablet using a Survey Monkey data collection instrument. Each assessment will have four sections:

1. **Initial waiting room conditions**
2. **Systematic observation of all waiting room patients during one video cycle**
3. **Systematic observation of select waiting room patients during the next video cycle**
4. **Summary comments**

The observer will complete one assessment for every two cycles of the video. The observer will continue to complete the assessments until he/she has completed an 8-hour shift (6-8 assessments).

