**2. Systematic observation of waiting room patients**

Observer will begin this observation at the beginning of the video (i.e. video Opening shots and title) and will continue this observation through each segment of stories or animation in the video for one full cycle of the video. The observer will concentrate on patients who were not present during the previous video cycle. The observer will look around the room going from patient to patient, covering all patients that can be seen from his/her vantage point, to observe their reactions. The main objective of this section is to note any points in the video that seemed to hold patients’ attention, not hold attention, or elicit a positive or negative reaction such as laughter, discussion, or disengagement with the video. Patients who are multi-tasking while watching the video will be considered to be watching the video. Observer will use the time during the credits to note additional general observations for this cycle.

The variables collected in this section include:

- Number of patients by apparent age
- Number of patients by apparent race/ethnicity
- Number of patients by apparent gender
- Number of patients who have a clear view of a video monitor
- Number of patients in the waiting room that the observer can see (to measure engagement with video)
- Number of patients in the waiting room who were present for the previous cycle.
- General observations about engagement with all video segments for all patients for this cycle

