### 2h. Story 1: Enter general comments and any information relevant to patient engagement that you observed during this segment. For example, did one part of the story seem to be particularly engaging or not engaging? Did this seem to vary by race/ethnicity, age, or gender?

|  | ▲ |
| --- | --- |
|  |  |
|  | ⯆ |

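### The sampling section's 32 observational assessments exceed the 24 that three sites allow, and the all-patient half of the observation form does not systematically record the per-segment counts the analysis plan names

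*Protocol*

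**What the plan says.** **Number of assessments.** The study design section fixes the sites: "The three HIV/AIDS treatment facilities where the beta-testing will take place are" the Atlanta, Huntsville and Miami clinics. The sampling section (III.B) covers patients "present in the waiting room during the 1 day of observation at each facility" and continues: "A maximum of 8 observational assessments will be done at each facility (32 total assessments". The bias section (III.D) gives another total: "for a total of 24 assessments and an estimated 192 to 336 patients observed across all three facilities". Appendix 2 has the observer work "until he/she has completed an 8-hour shift (6-8 assessments". Item 1a of the form in Appendix 3 offers four clinics.

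**Planned analysis.** The data analysis plan (III.D) says that the all-patient half of each assessment is analysed qualitatively for each of six segments, with codebooks written once the data are in. It also names numerical targets: "Content analyses of the observations will look for number of patients who watch or ignore the segment". It defines the frequency of disengagement as a number of patients per segment, to be related to those patients' apparent characteristics. The select-patient half is analysed in the same way.

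**What is recorded.** Appendix 2, section 2, lists the engagement variable for the all-patient half as: "General observations about engagement with all video segments for all patients for this cycle". On the form, each of items 2g-2l reads: "Enter general comments and any information relevant to patient engagement that you observed during this segment", followed by example questions, one of which asks whether engagement varied by race/ethnicity, age or gender.

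**The concern.** The two totals for the observation sample disagree, and the one in the sampling section cannot be reached with the sites named.

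The second issue is a mismatch between instrument and analysis. The plan names counts of patients per segment, but no field in the all-patient half asks for one. There is a single observation day per site, and codebooks are written afterwards. A count that the observer did not write down cannot be recovered at the coding stage. The bias section also means to offset expectancy effects by looking at segments in which many patients were disengaged. For the room as a whole, that needs some per-segment number.

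**Working it through.** **1. Total assessments**

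Inputs: 3 facilities (study design); at most 8 assessments per facility and 32 in total (sampling); 6-8 per 8-hour shift, one shift per site (Appendix 2); 24 in total and 192-336 patients (bias section).

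- Attempt to reproduce the stated 32: 3 × 8 = 24. It does not reproduce.
- 4 × 8 = 32. The figure fits only a four-site count, as does the fourth clinic in item 1a.
- Lower end: 3 × 6 = 18, so the feasible range is 18-24.
- Excess over the maximum: (32 − 24) / 24 = 33%.
- Cross-check against the patient estimate: 192 / 24 = 8 and 336 / 24 = 14, whole numbers per assessment. With 32 assessments they would be 6 and 10.5. The patient estimate therefore appears to rest on 24.

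**2. Form against analysis plan**

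| Quantity named in the analysis plan | All-patient half (items 2a-2l) | Select-patient half (items 3a-3s) |
| --- | --- | --- |
| Number watching or ignoring, per segment | No number field; free text | Amount watched, per patient and segment |
| Positive or negative reaction, per segment | No number field; free text | Tick boxes, per patient and segment |
| Demographics of disengaged patients | Room totals for the cycle (2c-2e), plus a free-text prompt on variation | Recorded per patient (3a), on the same form as that patient's reactions |

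The all-patient half has no structured engagement field for any segment. It has 6 text boxes per assessment, so up to 24 × 6 = 144 text entries.

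**3. Patients with structured engagement data, at 24 assessments**

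- Initially selected: 24 × 4 = 96 patients, giving up to 96 × 6 = 576 patient-segment records.
- With all four replacements used every time: 24 × 8 = 192 patients. Replacements are watched for only part of a cycle.
- At 18 assessments the initially selected number is 18 × 4 = 72.

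**The case against.** The strongest reply is that the all-patient half is declared qualitative. Prompted text boxes, content analysis and later codebooks fit together. Appendix 2 says that the main purpose of this section is to note the points that held or lost attention, and the study calls itself developmental. No test, threshold or power statement uses these counts. This stands, and it limits the point in four ways.

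- A reader might infer that the watch/ignore and who-disengages analyses cannot be run at all. The documents do not support that. A qualitative version can be run from the text, and an observer may volunteer counts. What lacks support is a reliable numerical frequency.
- A reader might infer that nothing links disengagement to demographics. Each of items 2g-2l asks about exactly that, and the summary comments in Appendix 2 ask again. Only a structured cross-count is absent.
- A reader might infer that most observed patients contribute nothing: 1 − 96/192 = 50% to 1 − 96/336 = 71%. That leaves out replacements. If all were used, the range would be 1 − 192/192 = 0% to 1 − 192/336 = 43%. It also treats patients described in text as lost, contrary to the qualitative plan. No firm percentage can be given.
- A reader might infer that 32 damages the sample-size case. The power calculations concern the medical-record outcomes and do not use it. The bias section already has the right total, and the fourth clinic is an unused option in what the appendix labels a simulated display.

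One part of the reply does not stand: that the select-patient half makes good the gap. Its patients must have a clear view, are picked with diversity in mind, and should be people who were not present in the preceding cycle where enough are available. They can carry their own numerical analysis, but they do not supply counts for the whole room.

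**Conclusion.** Both parts hold, within limits.

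- The stated total of 32 is wrong as written. The maximum is 24, and 18-24 is the range at the shift workload given in Appendix 2. This follows from the Protocol's own figures with no outside assumption. The error describes the observation sample only.
- For the all-patient half, the per-segment numbers of patients watching, ignoring or reacting negatively, and their cross-tabulation by demographics, are named in the analysis plan but not systematically captured. Qualitative analysis of that half is unaffected. Structured data are confined to 96 initially selected patients, up to 192 with every replacement, assuming 24 assessments and four patients available each time.

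This is not detail that could be left to a later analysis plan. The full form is part of the Protocol, and what it omits on the observation day stays missing.

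**What to change.** - In the sampling section, change 32 to 24 total assessments (18-24 at 6-8 per shift), and remove the fourth clinic from item 1a. Cost: text edits only.
- Add four number boxes to each of items 2g-2l: watching, not watching, positive reaction, negative reaction. Bring the variable lists in III.C and Appendix 2, section 2, into line.
- Keep demographic variation in this half as the existing free-text prompt.
- Edit the data analysis plan so that the numerical relation between disengagement and apparent demographics is drawn from the select-patient half only, and the all-patient half treats it qualitatively.

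The cost is 4 × 6 = 24 short entries per all-patient cycle, made by one observer who is also scanning the room. Splitting the not-watching count by the form's gender (3), age (3) and race/ethnicity (7) categories is not advised. It would mean 4 + 13 = 17 boxes per segment, or 102 per cycle, which could degrade the observation. The form must be changed before observation begins in June 2016.
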